#### Secondary indicator

2.7.2

The secondary outcomes encompass the Mini-Mental State Examination (MMSE) score, EORTC QLQ-C30 score, and the expression levels of inflammatory cytokines [tumor necrosis factor-*α* (TNF-α), interleukin-2 (IL-2), interleukin-4 (IL-4), interleukin-5 (IL-5), interleukin-6 (IL-6), interleukin-8 (IL-8), interleukin-10 (IL-10), interleukin-17 (IL-17), interleukin-1β (IL-1β), interleukin-12p70 (IL-12p70), interferon-*γ* (IFN-γ), and interferon-α (IFN-α)].

##### MMSE

2.7.2.1

The MMSE is widely employed as a screening tool to detect mild cognitive impairment through brief assessments (39). This questionnaire encompasses simple tasks across various domains: temporal and spatial orientation, word list repetition, arithmetic operations such as serial subtractions of seven, language comprehension and usage, and fundamental motor skills. A higher score indicates better overall cognitive function, with a score of 27–30 indicating normal function, 21–26 indicating mild impairment, 10–20 indicating moderate impairment, and 0–9 indicating severe impairment. For a respondent with a high-school education and above, a score lower than 24 indicates possible cognitive impairment, and for a respondent with only a primary school education or who is illiterate, the cutoff scores are, respectively, 20 and 17. A lower score indicates a higher degree of cognitive impairment (40). The MMSE will be utilized to evaluate mild cognitive impairment in patients at baseline, upon completion of treatment, and during the follow-up period.

##### European organization for research and treatment of cancer QLQ-C30 (EORTC QLQ-C30)

2.7.2.2

The EORTC QLQ-C30 is a patient-reported outcome measure comprising 30 items designed to evaluate the health-related quality of life in cancer patients.

The EORTC QLQ-C30 is transformed into 15 scales using a standardized scoring methodology. It encompasses 5 functional scales, 8 symptom scales, an item evaluating financial difficulty, and one global health status scale. The functional scale incorporates physical, role, emotional, cognitive, and social functioning. The symptom scales or individual items comprise fatigue, pain, nausea/vomiting, dyspnea, insomnia, appetite loss, constipation, and diarrhea (41). The summary score is determined using the transformation of all the EORTC QLQ-C30 scale and item scores, however not including global health status and financial impact. For the functional and the global health status, a higher score indicates better health. For the symptom scales, a higher score indicates more symptom burden. The EORTC QLQ-C30 summary score is calculated as the mean of the combined 13 EORTC QLQ-C30 scale and item scores (excluding the global health status and financial impact), with a higher score indicating a better health-related quality of life (42). The EORTC QLQ-C30 score will be evaluated at baseline, upon treatment completion, and during the follow-up period to assess health-related quality of life.

##### Expression of inflammatory cytokines

2.7.2.3

To investigate the potential mechanisms of acupuncture in patients with triple-negative breast cancer chemotherapy-related cognitive impairment, this study will select 15 patients from each the verum acupuncture group and the sham acupuncture group and collect cytokine data at baseline, at the end of treatment, and during the follow-up period. The equipment utilized for this purpose comprises 12 test kits for cytokines (magnetic particle luminescence). On the day of the cognitive function evaluation, 3 mL blood samples will be drawn from the patients and stored in a serum separation tube. All samples will be centrifuged for 5 min at 1500 RPM. Subsequently, the plasma and serum will be processed, and the supernatants stored at −20°C until analysis. The following blood biomarkers will be measured by experienced technicians blinded to the clinical data: human serum TNF-*α*, IL-2, IL-4, IL-5, IL-6, IL-8, IL-10, IL-17, IL-1β, IL12-P70, IFN-*γ*, and IFN-α. Testing will be conducted in strict accordance with the reagent instructions. Twelve test kits for cytokines (magnetic particle luminescence) will be prepared. The reagent kit will be brought to room temperature prior to the experiment (18–28°C). Standards and quality control solutions will be prepared according to the manufacturer’s instructions. Using immunoassay and multiplex detection techniques to detect cytokine concentrations. Then the samples and standards will be separately pipetted into designated reaction wells. The microplate will then be placed on a magnetic plate and allowed to stand for 1 min. After three repetitions of washing cycles, perform machine testing. All samples will be evaluated in duplicate and averaged. These measures will be assessed at baseline, at the end of treatment, and during the follow-up period. The detailed outcome assessment time points are provided in Table 1.

### Safety assessments

2.8

The study will meticulously document any adverse events occurring during the treatment period, including their characteristics, timing, severity (mild, moderate, or severe), duration, progression, and outcomes. All adverse events, regardless of relation to the acupuncture cure, are meticulously documented and evaluated by the researchers on the adverse event form at each assessment. The causal relationship between adverse events and acupuncture treatment will be promptly assessed, and the correlation between them will be analyzed (unrelated, possibly related, or definitely related). Appropriate interventions will be implemented immediately to ensure participant safety, and these measures will be recorded. Common adverse events associated with acupuncture include pain, bruising, and localized swelling at the needle insertion sites, which typically resolve spontaneously with rest or compression. Serious cases should to be reported to the Medical Ethics Committee of Beijing Hospital of Traditional Chinese Medicine, Capital Medical University within 24 h and their participation in the trial will be aborted. Upon occurrence of an adverse event, participants will immediately receive appropriate treatment and decide whether to withdraw from the trial at their own discretion. Participants who abort the trial will continue to be investigated and followed up, and the results will be recorded accordingly.

## Data management and quality control

3

A printed Case Report Form (CRF) will be utilized for clinical data management. The recorded clinical data are considered original and immutable. A designated researcher on the team will maintain custody of the form, with access restricted to authorized researchers. Upon completion of the trial, designated researchers will input the clinical data into a computer system. The sponsor should keep CRF for 5 years after the end of the research. All data will be stored with the principal investigator in a password-protected computer for a period of 5 years. All soft copies of the data will be permanently deleted from the computer once the data storage time is over or at the conclusion of the study. According to the terms of informed consent, unless the subject’s consent is obtained, all the subject’s personal information is confidential and will not be disclosed to the public. The results of this study will be published in peer-reviewed journals and posters or oral presentations at relevant conferences. All data will be available beginning 3 months and ending 3 years after publication of the results. The trial data will be available from the corresponding author upon reasonable request.

## Statistical analysis

4

The statistical analysis will be conducted using Microsoft Excel 2016 and SPSS 25.0 statistical software (IBM Corporation, Armonk, NY, United States). An independent statistician, blinded to group assignment, will perform the statistical analysis. All data will be analyzed according to the intention-to-treat (ITT) protocol, regardless of adherence, provided participants receive at least one acupuncture treatment session and complete a baseline assessment of the primary outcome. Missing values will be imputed using the last observation carried forward method. The per-protocol (PP) population, comprising all randomized patients who completed more than 80% of the treatment procedure, will also be analyzed. All statistical tests will be two-sided, with a *p* value of <0.05 considered statistically significant. Categorical variables will be reported as medians (interquartile ranges), while continuous variables with normal distributions will be presented as means ± standard deviations. The chi-square test or Fisher’s exact test will be employed to compare dichotomous data from baseline demographic and clinical information. Measurement data include various scale scores and indicators of inflammatory cytokine expression levels. For normally distributed variables, an independent samples t-test will be used for between-group comparisons, and a paired samples t-test for within-group comparisons before and after therapy. Comparisons at multiple time points will be made using repeated-measures analysis of variance. The Mann–Whitney U test will be utilized for non-normally distributed variables in intergroup comparisons to analyze changes in efficacy outcomes. The comparison of multiple time points will be based on the generalized estimating equation (GEE). Multiple linear regression analysis will be employed to examine correlations between clinical efficacy and inflammatory cytokines.

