### Randomization and blinding

2.3

A computer-generated block randomization with 1:1 allocation will be used to assign 50 eligible participants. An independent statistician at the Beijing Hospital of Traditional Chinese Medicine, Capital Medical University will implement the randomization procedure using SPSS 25.0 statistical software (IBM Corporation, Armonk, NY, United States), employing randomly permuted blocks to ensure allocation concealment. The allocation information will become available only after the randomization procedure. Subsequently, a second individual will employ an opaque envelope containing a randomly sorted distribution card to assign patients to either the verum acupuncture group or the sham acupuncture group, based on their hospital visits. The research assistant responsible for randomization and acupuncturists are not blinded to the participant allocation. The data analysts and outcome assessors will not be aware of the allocated group.

To mitigate potential expectations regarding acupuncture treatment, patients will be informed that they will randomly receive one of two different acupuncture regimens. It is not possible to blind participants, owing to the different acupuncture points of the two groups. To minimize potential communication and interaction among participants, each patient will receive individualized acupuncture treatment and follow-up at separate times in distinct rooms. Due to the inherent nature of acupuncture intervention, blinding the acupuncturist is not feasible. Blinding will be applied to the outcome assessment. Data analysts and outcome evaluators will be blinded to the treatment allocation. Furthermore, to maintain the integrity of the study, communication between acupuncturists, participants, and outcome evaluators will be carefully structured to prevent any exchange of information. The assessor will be arranged to conduct assessment on different days from acupuncture treatment to avoid cross communication among the assessor, acupuncturists, and participants. The assessor will also be instructed not to acquire participants’ treatment information and their needling feelings. Prior to analysis, all data will be anonymized to ensure objectivity.

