### Written informed consent

2.4

For any TNBC participants who meet the inclusion and exclusion criteria, they will be approached to participate in the study by one of the investigators from the study team. All participants will be provided with a written copy of the consent form detailing their random assignment to either verum acupuncture or sham acupuncture, as well as the potential benefits and risks. The investigator will be responsible for ensuring that the patient completely understands the potential risks and benefits of participating in the study and for answering any questions the patient may have. Responses will be in a language that the subject understands, with translation and visual aids as necessary. Participants can contact the investigator at any time to inform them of their decision and to ask any questions about the study through outpatient or inpatient visits, email contact, phone contact, WeChat contact or other web-based contacts. Prior to participating in the research, all participants will voluntarily sign the informed consent form. Withdrawal conditions: (1) Participants may choose to withdraw at any stage of the trial if they prefer not to receive the assigned treatment. (2) Participants must withdraw if adverse events (AEs) occur that require their withdrawal from the trial. (3) Participants are unable to complete protocol-specified procedures during the treatment or follow-up phases. (4) Participants can withdraw from the study for any reason. Participants will be asked if they agree to use their data for further analysis and sharing with researchers relevant to this study should they choose to withdraw from the trial.

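### The set labelled intention-to-treat leaves out randomised patients who receive no session, in a trial where the acupuncturists and the randomising assistant know the arm

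*Protocol article*

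**What the plan says.** The Statistical analysis section states: "All data will be analyzed according to the intention-to-treat (ITT) protocol, regardless of adherence". The same sentence then sets two entry conditions: "provided participants receive at least one acupuncture treatment session and complete a baseline assessment of the primary outcome". Missing values are imputed by last observation carried forward. The only other set is per-protocol, meaning more than 80% of the treatment procedure completed, which is narrower.

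On who knows the arm, Randomization and blinding says:
- "The research assistant responsible for randomization and acupuncturists are not blinded to the participant allocation".
- Of participants, "It is not possible to blind participants, owing to the different acupuncture points of the two groups", although "patients will be informed that they will randomly receive one of two different acupuncture regimens".
- "The data analysts and outcome assessors will not be aware of the allocated group".

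On leaving the trial, Written informed consent says "Participants may choose to withdraw at any stage of the trial if they prefer not to receive the assigned treatment" and adds that those who withdraw are asked whether their data may still be used. The Safety assessments section says "Participants who abort the trial will continue to be investigated and followed up, and the results will be recorded accordingly".

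Table 1 places both randomisation and the baseline MoCA at week 0.

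**The concern.** Receiving no session at all is the extreme of non-adherence. A rule that removes such patients contradicts the promise to analyse regardless of adherence, and the intention-to-treat label does not describe the set.

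Leaving out patients who never start is usually defended on the ground that starting cannot be influenced by knowledge of the arm. That defence is not available here. The acupuncturists deliver the first session and know the allocation, as does the assistant who handles randomisation. Whether a session is arranged, postponed or never held can therefore differ by arm. If it does, the comparison of those who started is no longer the randomised comparison. Blinded assessment does not repair this, because the patient has been lost before the outcome is assessed.

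**Working it through.** **Inputs.** From Sample size calculation: 25 per arm, effective rates 58.33% (verum) and 13.72% (sham), two-sided alpha 0.05, power 0.90, 20% attrition. From Primary indicator: improvement rate = (post − pre)/pre × 100%; a patient counts as effective at 12% or more, and a rate from −12% to below 12% is classed as invalid. From Statistical analysis: last observation carried forward.

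**1. The plan's own figure.** Unpooled normal formula: n = [p1(1 − p1) + p2(1 − p2)] × (1.960 + 1.282)² / (p1 − p2)² = 0.3614 × 10.507 / 0.1990 = 19.08, rounded up to 20. Then 20/(1 − 0.20) = 25 per arm. The stated size reproduces and is not in dispute.

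**2. How a non-starter would be classified.** With a baseline MoCA and no later value, the baseline is carried forward: post = pre, so the improvement rate is 0/pre = 0%. That lies in the invalid band, so the patient is a non-responder. With r responders among 25 and k such patients removed, the arm's rate goes from r/25 to r/(25 − k). This is higher whenever r > 0 and unchanged when r = 0.

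**3. Size on one arm's rate (assumed counts).** One patient is 1/25 = 4% of an arm.
- r = 13, k = 3: 13/25 = 52.0% becomes 13/22 = 59.1%, a gain of 7.1 points.
- r = 14: 14/25 = 56.0% becomes 58.3%, 60.9% and 63.6% for k = 1, 2 and 3.

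**4. Size on the comparison (assumed counts, non-starters in the verum arm only).**

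| All randomised | Non-starters dropped | Test | p, all randomised | p, dropped |
|---|---|---|---|---|
| 11/25 v 4/25 | 11/24 v 4/25 | Fisher | 0.062 | 0.032 |
| 10/25 v 4/25 | 10/24 v 4/25 | chi-square, uncorrected | 0.059 | 0.047 |
| 13/25 v 3/25 | 13/22 v 3/25 | Fisher | 0.0054 | 0.0016 |

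The first two rows were chosen close to the threshold and show that one exclusion can be enough to cross 0.05. The third has rates nearer those planned, and the conclusion does not change. Non-starters in the sham arm would raise the sham rate and shrink the difference instead.

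**5. Power after the change.** If non-starters stay in as non-responders, power at 25 per arm (pooled normal formula, planned rates among starters) is 93.3% with none, 91.5% with 4% in each arm and 89.4% with 8%. The non-starter shares are assumptions.

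**The case against.** **The participants' route.** A reader might infer that unblinded participants will leave before treatment because they dislike their arm. The documents do not support that as the main route. The stated reason that participants cannot be blinded is the needling points, which they meet at the first session; by then the one-session condition is satisfied and they stay in the set. They are told only of two regimens and are treated separately. The permission to withdraw applies at any stage and does not show that patients learn their arm beforehand. The route is not wholly closed, since the consent form names verum and sham and nothing says expressly that the arm is withheld until needling. The documented route before session 1 is still mainly the unblinded staff.

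**Which staff.** It would also be wrong to read this as all staff being unblinded. Outcome assessors and data analysts are blinded, and the set is formed by an objective rule. That stands, but it does not protect the event the rule depends on, which is whether a session was given.

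**The baseline condition.** One might want to strike out both entry conditions. The baseline MoCA has to stay: the primary outcome divides by it, and without it there is nothing to carry forward. Since it is due at week 0, it should exclude almost nobody.

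**Size.** No non-starter rate is given; the 20% is overall attrition. Both arms are needled on the same schedule, and nothing points to more non-starters in one arm. Non-starting for reasons unrelated to the arm, such as travel, need not bias the comparison. All of this stands and limits the likely size. It does not make the label correct.

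**Conclusion.** The point holds as a mislabelled set that is open to arm-related exclusion. That the set is not intention-to-treat follows directly from the article's wording and rests on no assumption. That exclusions can depend on the arm follows from the stated unblinding of the acupuncturists and the randomising assistant. That they will do so is not shown, and a reader should not infer a demonstrated bias.

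The upward direction within an arm rests on non-starters having no later MoCA. If a non-starter is followed up and has an observed week-8 score, that score decides, and the effect of dropping the patient could go either way. The sentence on continued follow-up stands among the safety procedures and does not clearly cover patients who never begin.

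The size is 4% of an arm per patient. The number of non-starters is unknown and may be zero, in which case the two sets coincide. The matter should be corrected but does not by itself undermine the trial.

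**What to change.** In the Statistical analysis section, define the main intention-to-treat set as all randomised patients in their allocated arm. Use the observed week-8 MoCA where there is one, and otherwise the plan's stated imputation from the week-0 MoCA, which remains necessary to define the outcome. Exclude only patients who refuse use of their data, and report their number by arm. Keep the present at-least-one-session set as a sensitivity analysis under the name modified intention-to-treat, and report the number of non-starters by arm.

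The cost is a few lines of text. The sample size stays at 50. Trial status describes recruitment as continuing, with 20 patients enrolled, so the article leaves room to make the change before analysis. The downside is that the estimate may be slightly less favourable, with the modest loss of power shown above if some patients never start.

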To the best of our knowledge, cytokines may play a crucial role in the pathogenesis of CRCI. Previous studies have shown that cytokines show different temporal trends during and after chemotherapy, and are associated with specific areas of cognitive impairment (29, 30). IL-6 levels show a biphasic pattern, with consistently increasing concentrations from the start of chemotherapy to 6 months post-chemotherapy, followed by a gradual decline over time after 6 months (29). In contrast, IL-1β and IL-4 levels remain significantly elevated after chemotherapy and are associated with long-term deficits in verbal memory and executive function (30, 31). IL-7 and IL-10 show transient suppression early in the course of chemotherapy, with recovery trajectories associated with improved verbal fluency (30). Several scholars have proposed that a quantitative cytokine level balance or ratio is also associated with the development of CRCI, that cytokines present at different concentration levels in different regions of the brain, and that memory function correlates with optimal concentration levels of specific cytokines (30). TNF-*α* is associated with acute cognitive trajectories (32), and IL-6 and IL-8 are associated with persistent cognitive trajectories (33). Elevated concentrations of IL-6 and IL-1β may result in a decrease in reaction speed and perceptual functioning (33). IL-4 has a protective effect on reaction speed and the higher the concentration, the better the learning ability (32).

However, no study has yet been conducted to elucidate the underlying mechanisms of acupuncture for CRCI based on cytokine activity. Therefore, we will conduct a randomized controlled clinical trial to evaluate the efficacy and safety of acupuncture for the treatment of CRCI in patients with TNBC. This study aims to provide high-level evidence supporting the potential therapeutic mechanisms of acupuncture. Specifically, we seek to elucidate the therapeutic mechanisms of acupuncture for CRCI by examining the expression levels of inflammatory cytokines.

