#### Primary indicator

2.7.1

The primary outcome measure is the total effective rate of the 8-week MoCA score. Changes in the MoCA score from baseline to the end of treatment and the follow-up period will assess patients’ cognitive function. The MoCA, a concise cognitive function assessment tool comprising 12 items, was developed by Nasreddine in 2005. It evaluates visuospatial abilities, executive function, short-term memory, language, and orientation to time and place (19). The MoCA test has a maximum score of 30 points, with scores between 21 and 26 indicating mild cognitive impairment. For individuals with 12 or fewer years of education, one point is added to the final score (37). The lower the score, the worse the cognitive function. To evaluate cognitive function, the MoCA score and total improvement rate will be assessed at baseline, at the conclusion of treatment, and during the follow-up period. The score of the MoCA, the absolute changes in scores from baseline to the end of treatment, and the follow-up period will be recorded. The minimum clinically significant difference of MoCA is 1.22 points (38). Improvement rate = [(posttreatment score − pretreatment score)/pretreatment score] × 100%. The curative effect is judged as follows: Significantly effective: Improvement rate≥20%; Effective: 12% ≤ Improvement rate<20%; Invalid: −12% ≤ Improvement rate<12%; Total effective rate according to the formula: (Significantly effective + Effective)/Total cases×100%.

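### Carrying the last observation forward makes every patient without a week-8 MoCA a non-responder by default, assumes persistence to week 14, and does not match the sample size

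*Protocol article*

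**What the plan says.** Section 4 (Statistical analysis) gives a single missing-data rule, with no exception by outcome: "Missing values will be imputed using the last observation carried forward method". The intention-to-treat set keeps everyone, "provided participants receive at least one acupuncture treatment session and complete a baseline assessment of the primary outcome". A per-protocol analysis is added for patients who completed more than 80% of treatment, but it handles missing values no differently.

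Section 2.7.1 (Primary indicator) states: "The primary outcome measure is the total effective rate of the 8-week MoCA score". On timing, "the MoCA score and total improvement rate will be assessed at baseline, at the conclusion of treatment, and during the follow-up period". Table 1 puts MoCA, MMSE, QLQ-C30 and cytokines at weeks 0, 8 and 14 only. (Section 2.5.1 gives week 16 for the last assessment; the point here is the same either way.) The formula is "Improvement rate = [(posttreatment score − pretreatment score)/pretreatment score] × 100" per cent. A change from −12% to below 12% is classed as invalid, that is, not a response.

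On what happens to patients who leave, Section 2.4 (Written informed consent) lists as withdrawal condition (3): "Participants are unable to complete protocol-specified procedures during the treatment or follow-up phases". Section 2.8 (Safety assessments) says: "Participants who abort the trial will continue to be investigated and followed up".

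**The concern.** With no visit between baseline and week 8, the last observation for a patient who misses week 8 is the baseline itself. The rule then decides the primary outcome for that patient: non-response. That may be a reasonable convention, but here it is a side effect of the imputation rule and not a stated definition.

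For week 14, the rule copies the week-8 value. Whether any benefit lasts after treatment ends is the question of the follow-up phase, so the rule supplies part of the answer.

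For scores and cytokines, copied values enter t-tests, repeated-measures ANOVA and GEE as though measured. The uncertainty of the imputation is ignored, and a copied value contributes an exact zero change.

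Two things are at stake. One is whether the planned power describes the planned analysis. The other is whether a difference in dropout between arms could appear as a difference in effect. Participants are not blinded (Section 2.3), and the two needling procedures differ in depth and manipulation (Sections 2.5.1 and 2.5.2), so unequal dropout is possible.

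**Working it through.** **Inputs.** From Section 2.6: response 58.33% verum and 13.72% sham, two-sided alpha 0.05, power 0.90, attrition 20%, 25 per arm. From Sections 2.7.1 and 4: the response definition, the analysis set and the imputation rule. The unequal dropout splits and the 35% and 36% null rates are assumptions.

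**1. The plan's own figure.** Two proportions, unpooled variance:

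n = [p1(1−p1) + p2(1−p2)] × (1.960 + 1.282)² / (p1−p2)²
= (0.2431 + 0.1184) × 10.507 / 0.4461² = 19.1, rounded up to 20.
20 / 0.8 = 25 per arm, 50 in total, as stated. The calculation therefore treats the 20% as absent from the analysis.

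**2. What the rule does to one patient.** Without a week-8 score, post = pre, so improvement = (pre − pre)/pre = 0%. This lies between −12% and 12%, so the patient is a non-responder and stays in the denominator.

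**3. Equal 20% dropout.** Assume no week-8 MoCA for these patients, who would otherwise have responded like completers. The observed rate is p(1−d):

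- Verum: 0.5833 × 0.8 = 46.7%
- Sham: 0.1372 × 0.8 = 11.0%
- Difference: 35.7 points, against 44.6 planned

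Power with 25 per arm, same unpooled formula: SE = √[(0.2489 + 0.0977)/25] = 0.1177; 0.3569/0.1177 − 1.960 = 1.07, giving about 86%. The pooled formula gives 82% and exact Fisher 73%. Holding 90% would need about 29 per arm (unpooled) or 32 (pooled).

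**4. Unequal dropout at the planned rates (assumed splits, mean 20%).**

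| Verum / sham dropout | Difference (points) |
|---|---|
| 30% / 10% | 28.5 |
| 20% / 20% | 35.7 |
| 10% / 30% | 42.9 |
| 40% / 0% | 21.3 |
| 0% / 40% | 50.1 |

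The difference exceeds 44.6 only if 0.1372 × sham dropout is larger than 0.5833 × verum dropout, that is, if sham dropout is more than 0.5833/0.1372 = 4.25 times verum dropout.

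**5. No true effect, assumed 10% verum and 30% sham dropout.** Spurious difference in favour of verum = p × (0.30 − 0.10):

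| True response in both arms | Spurious difference |
|---|---|
| 13.72% | 2.7 points |
| 35% | 7.0 points |
| 58.33% | 11.7 points |

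The exact type I error of the chi-square test with 25 per arm is 6.2% at 13.72%, 9.1% at 36% and 15.7% at 58.33%, against 5.4%, 5.7% and 6.1% with no dropout. With Fisher's test under the same split it is 1.5%, 4.4% and 9.6%.

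**The case against.** **Counting missing as failure is a legitimate responder definition.** This stands. With equal dropout it is also conservative for a superiority claim. But the protocol does not declare it, and the sample size does not allow for it.

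**Unequal dropout is hypothetical.** This also stands. Section 2.6 gives one attrition figure and nothing in the document predicts a split. A reader might infer that the rule will favour verum. The document does not support that: at its only null-type rate, 13.72%, a 10%/30% split adds 2.7 points, and at the planned rates most splits shrink the effect. The larger null figures need higher assumed response rates.

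**Section 2.8 may limit the problem.** If those who abort are still assessed at week 8, they need no imputation and the figures above are upper bounds. But a reader should not infer that Section 2.8 secures the week-8 MoCA: it stands under safety and names no outcome visit. Section 2.4 points the other way for patients who cannot complete procedures.

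**The cytokine rationale.** A reader might infer that the rule contradicts the Introduction, which says "IL-6 levels show a biphasic pattern, with consistently increasing concentrations from the start of chemotherapy to 6 months post-chemotherapy". That goes too far. The same text describes a later gradual decline in IL-6, and IL-1β and IL-4 remaining raised. Entry is allowed up to 3 years after chemotherapy, and observation lasts 14 weeks. Assuming no change in cytokines is a weak assumption, not a contradiction.

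**Multiple imputation has its own cost.** It assumes data are missing at random and would rest on about 20 completers per arm. This is a fair limit and a reason to keep the predictor set small. That copied values distort standard errors follows from treating them as measured; the size was not estimated.

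**Conclusion.** The concern holds in a limited form. The rule is fixed in the text and is not a detail left to an analysis plan that is not shown. It makes patients without a week-8 MoCA non-responders by default, presumes persistence to week 14, and treats copied scores and cytokines as data.

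The firmest numerical consequence is the mismatch with the sample size: a 35.7-point expected difference and about 86% power, where 44.6 points and 90% were planned. It rests on two assumptions: that the 20% attrition means no week-8 MoCA, and that dropouts would otherwise have responded like completers. It needs no difference in dropout between arms.

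Bias from unequal dropout is a conditional risk: 2.7 to 11.7 spurious points under an assumed 10%/30% split, depending on the common response rate. For the responder outcome, the choice of lead analysis is partly convention. The clearer gain from a change lies in the score and cytokine analyses, and in having a primary analysis that does not fix dropouts as failures.

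**What to change.** Remove last observation carried forward from Section 4 and replace it as follows.

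- **Scores and cytokines:** a likelihood-based mixed model on all observed data, without imputation, with cytokines suitably transformed.
- **Week-8 responder outcome:** multiple imputation of week-8 MoCA by arm, with a small predictor set such as baseline MoCA and MMSE. Response is derived from the imputed score. State the missing-at-random assumption.
- **Sensitivity analysis:** missing counted as not improved, stated as such.
- **Sections 2.4 and 2.8:** withdrawal condition (3) and the statement on following up those who abort must be reconciled, so that it is clear whether outcome assessments continue after withdrawal.

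The cost is mainly analysis text. Both methods are available in SPSS, which the plan already names. At the time of the article 20 of 50 patients were enrolled (Section 5), so the change can be made before unblinding. The downside is reliance on missing at random with about 20 completers per arm, which the sensitivity analysis helps to bound.
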